### Participant timeline

Within 72 h after hospital admission, one buccal and rectal swab will be collected for analysis of the microbiome. Patients will be followed up until their discharge and categorization into mild, moderately severe and severe AP will be performed at the day of discharge.

### Sample size

We calculate to include 400 patients in total (300 with mild pancreatitis (Atlanta I), and 100 with moderately severe or severe AP (Atlanta II–III). This sample size was calculated before enrolment. The sample size is based on the variability of the measured area under the curve (AUC), which is calculated for assessing the predictive accuracy of outcomes. Assuming a true AUC of 0.8, a total of 100 patients per group will provide a power of 85% (99%) when testing against the alternative of an AUC > 0.7 (0.6) at one-sided 2.5% significance level. A 95%-confidence interval for an AUC of 0.8 [0.735; 0.855] will have a total width of 0.12.

### Recruitment

AP patients will be usually treated on gastroenterology or surgical wards. Thus, all participating centers will have access to AP patients on their wards. Furthermore, there is a cooperation between the local principal investigators (PIs) and the emergency room, and PIs will be given immediate notice if patients will have to be directly submitted to IMC or ICU. Therefore, local PIs will be aware of most AP patients admitted to their centers and will be able to enroll them for this study after written informed consent.

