### Eligibility criteria

Patients with AP (2 out of 3 following diagnostic criteria: lipase > 3 × of upper limit (> 280U/l), abdominal pain, and imaging modalities (computed tomography (CT), magnetic resonance imaging (MRI) or ultrasound)) indicating AP will be included within 72 h after hospital admission. In our study, amylase elevation will not considered as a diagnostic criterion. In most cases, the first two criteria lead to the diagnosis of AP. Only in rare cases one of the above-mentioned imaging tools will aid to diagnose AP. Typical ultrasound features are: increased volume (> 2.4 cm in pancreas-body diameter), decreased echogenicity and peripancreatic fluid collection [22]. CT and the MRI indicate AP if parenchymal enlargement (diffuse or localized), alterations in density, diffuse margins, acute peripancreatic fluid collection and/or surrounding fat stranding are reported [23]. All recruited patients will sign the informed consent form before buccal and rectal swab collection. Pregnant women, patients < 18 years and patients who are incapable of giving consent will be excluded. The last-mentioned group includes patients who are not authorized to give consent due to psychological or other diseases. Patients who show signs of chronic pancreatitis (CP) on imaging will also be excluded.

The intake of antibiotic and probiotic medication will be recorded before the collection of the swabs and will not be considered as exclusion criteria. Patients will be categorized in 5 groups according to the time of antibiotic medication: current, within the last week, more than 1 week and less than 6 month ago, and more than 6 months ago. Together with other drugs and reported diseases the anti- and probiotic intake will be statistically associated with the orointestinal microbiome patterns and thus treated as potential confounder. Table 1 summarizes medical history and previous medication that is recorded for each patient.

**Table 1 Tab1:** Medical history and previous medication

Medical history	Previous medication
Cardiovascular diseases (e.g. coronary artery disease, peripheral artery disease, TIA, apoplex)	Metformin
Heart failure	Insulin
Diabetes mellitus	Other antidiabetics
Inflammatory bowel disease	PROTON-pump inhibitors (including occational intake)
Irritable stomach and/or bowel disease	Immune suppressors (including topical immune suppressors affecting intestinal tract)
Clostrioides difficile infection within last year	Antidepressants

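### Time from admission to swab can differ between Atlanta grades, in either direction, and is neither among the stated confounders nor in the stated tests

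*Protocol article*

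**What the plan says.** **Sampling window.** Participant timeline: "Within 72 h after hospital admission, one buccal and rectal swab will be collected". Eligibility criteria and Outcomes give the same limit. None of the three sets a target hour or a stratum within the window.

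**Route to the investigator.** Recruitment describes two routes. For patients on gastroenterology or surgical wards it says: "Thus, all participating centers will have access to AP patients on their wards". It adds a cooperation with the emergency room, under which "PIs will be given immediate notice if patients will have to be directly submitted to IMC or ICU". Eligibility criteria requires signed consent before either swab and excludes patients who cannot consent.

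**Confounders.** Eligibility criteria: "Together with other drugs and reported diseases the anti- and probiotic intake will be statistically associated with the orointestinal microbiome patterns". On that basis these factors are to be handled as possible confounders. On antibiotics and probiotics it says "The intake of antibiotic and probiotic medication will be recorded before the collection of the swabs", and one of the antibiotic timing groups is current use. It also says "Table 1 summarizes medical history and previous medication that is recorded for each patient". Time from admission to swab appears neither in the confounder statement nor in Table 1.

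**Tests.** Outcomes makes the association between microbial composition and the revised Atlanta class the primary endpoint. Statistical methods compares groups by t-test or ANOVA, rank tests, PERMANOVA with pairwise adonis, LEfSe and AUC. No term for swab time is named.

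**The concern.** The grade is assigned at discharge, but early severity is plausibly related to it. Early severity can also affect when the swab is taken: an immediate alert may bring it forward, and the need for consent from a very ill patient may delay it. If the flora changes over the first days in hospital, a difference in swab time between grades becomes a difference in measured flora between grades. Unadjusted tests cannot separate this from a severity effect.

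Both the primary association and the AUC are exposed. The bias can create a signature, enlarge a real one or hide one, depending on which grade is sampled later and which way a given taxon drifts.

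**Working it through.** **1. The plan's own figure.** Sample size states 85% power for a true AUC of 0.8 against 0.7, with 100 per group at one-sided 2.5%. The Hanley-McNeil standard errors are 0.0314 at 0.8 and 0.0368 at 0.7. On the logit scale:

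- distance: logit(0.8) − logit(0.7) = 1.386 − 0.847 = 0.539
- critical value: 1.96 × 0.0368/(0.7 × 0.3) = 0.343
- SE under the alternative: 0.0314/(0.8 × 0.2) = 0.196
- power: Φ((0.539 − 0.343)/0.196) ≈ 84%

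The stated figure reproduces and is not at issue. It assumes that the AUC measures severity alone.

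**2. Inputs for the bias.** From Sample size: 300 mild and 100 moderately severe or severe cases. Assumed, because the documents give neither: a linear drift of one marker in SD per hospital day, and a gap in mean swab time between the two groups. No true severity effect.

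**3. Simple calculation.** Shift = drift × gap. Spurious AUC = Φ(shift/√2). SE of the mean difference = √(1/300 + 1/100) = 0.1155. Rejection is for a two-sided 5% test of no difference.

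| Drift (SD/day) | Gap (days) | Shift (SD) | Spurious AUC | Rejection |
|---|---|---|---|---|
| 0.1 | 0.5 | 0.05 | 0.514 | 7% |
| 0.25 | 0.3 | 0.075 | 0.52 | 10% |
| 0.25 | 1 | 0.25 | 0.570 | 58% |
| 0.5 | 2 | 1.0 | 0.760 | about 100% |

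For the third row: 0.25/0.1155 = 2.165, and Φ(2.165 − 1.96) = 0.58.

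The second row allows for the alert reaching only part of the complicated group. If 30% of those 100 patients go directly to IMC or ICU and are swabbed a full day earlier (both assumed), the group gap is 0.3 × 1 = 0.3 day.

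**4. Check that respects the window.** Swab times were simulated as normal with SD 12 h, truncated to 0–72 h, again with no severity effect. The spurious AUC by realised gap, for drifts of 0.25 to 1.0 SD per day, was:

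- about 4 h: 0.51 to 0.55
- about 9 h: 0.53 to 0.60
- about 21 h: 0.56 to 0.71
- about 32 h: 0.59 to 0.81

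Rejection of AUC = 0.5 at one-sided 2.5% ran from 5.5% (4 h, 0.25 SD/day) to about 100%.

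**5. Direction.** With a true AUC of 0.70, a gap of about 21 h and 0.5 SD per day, the apparent AUC is 0.79 if the drift runs with severity and 0.59 if it runs against it.

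**6. Against the design's null values.** Under the formula in step 3, a spurious AUC of 0.6 needs a shift of 0.36 SD (√2 × 0.253), and 0.7 needs 0.74 SD (√2 × 0.524).

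**The case against.** **The alert may equalise capture.** Recruitment mentions the wards first and then adds the emergency-room arrangement, which reads as closing a gap for patients who bypass those wards. A reader might infer that investigators are notified only of IMC and ICU patients, and that mild short-stay patients are the ones most likely to be missed. The text supports neither. It does not say that ward patients are found or swabbed later, and it expects investigators to know of most AP patients. This objection stands, so the point rests on the open window and the missing adjustment, not on a proven delay.

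**The trigger is not the comparison.** Direct IMC or ICU admission is not the Atlanta grade assigned at discharge, so any gap caused by the alert is diluted. This stands; the 0.3-day row shows how far the effect can shrink. A two-day mean gap inside a 72 h window is hard to attribute to a notification.

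**The central spurious AUC is below both design nulls.** A value of 0.57 would not by itself pass a test against 0.6 or 0.7. This stands for a marker with no real effect. It does not protect the tests of association, nor a real but modest marker, which step 5 shows can move from 0.70 to 0.79.

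**Part of this is covered or may sit elsewhere.** Current antibiotic use is recorded and treated as a confounder. The 72 h limit implies that sites know admission and swab times. Table 1 is not the full dataset, and an analysis plan not shown could adjust for time. The Discussion also cites intraindividual stability of rectal swabs. These reduce the concern but do not remove it. The article itself states its confounders and tests, and swab time is in neither. It does not say that the stability was shown during an acute pancreatitis admission, or for buccal swabs.

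**Conclusion.** The point holds as a possibility left open by the stated plan. The window is wide, the route to sampling is partly linked to initial severity, and the severity comparisons as written do not account for swab time. The direction is undetermined.

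The size cannot be derived from the documents. It ranges from negligible (AUC about 0.51) upward, with about 0.57 at 0.25 SD per day and a one-day gap. These figures rest on a linear drift in a single marker and on assumed gaps. The wide range of rejection rates describes those assumptions and does not estimate this study's error rate. A reader might infer that a reported signature would be an artefact of hospital stay; the documents do not support that either.

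The reason to act is that the adjustment is nearly free and removes a plausible confounder.

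**What to change.** - Record the date and hour of admission and of each swab. Data management says that uploaded entries cannot be altered, so the fields should be in place before upload. For patients already enrolled, sites can look the times up in their own records.
- In Eligibility criteria, add hours from admission to swab to the stated confounders.
- In Statistical methods, include it as a covariate in the PERMANOVA, alpha-diversity and differential-abundance comparisons. Adjust the AUC for it, or do so as a sensitivity analysis, without crediting the discrimination of time itself to the microbiome.
- Report the distribution of hours to swab by Atlanta grade. If the grades overlap little, the adjustment rests on extrapolation and the report should say so.
- Optional: extend the emergency-room alert to every AP admission. The point does not depend on it, and it would add notices for investigators to handle.

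The cost is two time fields and one extra covariate. Clinical management is unchanged.

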## Methods: data collection, management, and analysis

### Data collection methods

The oral and intestinal flora will be collected from buccal and rectal swabs. Within three hours after collection swabs will be stored at − 80 °C. External centers will ship samples on dry ice to Goettingen. All wet-bench and bioinformatical analyses will be conducted in Goettingen with an established in-house workflow. First, DNA will be extracted by *PureLink™ Microbiome DNA Purification Kit* (Invitrogen) with a protocol modified according to International Human Microbiome Standards (IHMS). For sequencing Oxford Nanopore Technologies (ONT) MinION and GridION will be employed. ONT represents a method which is considered as the 3rd generation of sequencing. This approach offers two benefits: long reads and a potential real time sequencing. For metagenomic sequencing a minimum of sequencing depth is defined as 10,000 microbial reads for buccal swabs and 25,000 microbial reads for rectal swabs. Regardless of the origin, all 16S rRNA samples need at least 250.000 read counts per sample. These 3 cut-offs were determined by rarefaction curve derived from preliminary experiments. We also developed a bioinformatical pipeline. After basecalling, demultiplexing and trimming the fast5 files (default ONT output) using guppy version 4.4.2, the reads are classified by centrifuge [24]. This tool uses an indexing scheme based on the Burrows-Wheeler transform and the Ferragina–Manzini index. Centrifuge convinces with its high sensitivity though it produces a high rate of false positive reads. To overcome this problem we established an alignment control with minimap2 [25] and a consecutive python script which excludes low quality reads. Both programs are validated for long reads generated by ONT [26]. For the classification with centrifuge and the alignment control with minimap2, a comprehensive library derived from the nucleotide database will be applied containing all complete and incomplete genomes from the National Center for Biotechnology Information (NCBI). Low quality reads will be filtered if they do not pass the following quality criteria: Basecall quality score < 7, centrifuge quality score < 150, alignment score based on Smith Waterman Score < 1000 and an alignment coverage of 50%. Subsequent microbiome analysis such as calculating alpha and beta diversity will be conducted in R-Studio (version 3.6.3). Furthermore, with R the clinical metadata will be correlated to the microbial communities, statistics will be performed, and the graphs will be created. Figure 1 summarizes the study design. All acquired fastq files and the corresponding metadata will be publicly available via Qiita (https://qiita.ucsd.edu/). Before uploading, the human reads will be removed from fastq files using bmtagger.

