## Methods: participants, interventions, and outcome

### Study setting

This study is a multicentric prospective study initiated and coordinated from the University Medical Centre Goettingen and supported by the AG Pancreas of the German Society for Digestive and Metabolic Diseases (DGVS) and the European Pancreatic Club (EPC). To date, seven German University Hospitals (LMU Munich, Technical University Munich, Leipzig, Greifswald, Halle, Rostock, Goettingen) and one District Hospital (Hann. Münden) are actively recruiting patients. The principal investigator intends to include more centers across Germany and Europe. All collected samples will be sent to Goettingen where wet-bench and bioinformatical analyses will be conducted. The study was registered 2nd March 2021 (retrospectively) at the US National Library of Medicine at https://www.clinicaltrials.gov (NCT04777812).

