### Outcomes

This prospective translational study aims to evaluate the orointestinal microbiome as a potential biomarker for the course, severity and outcome of patients with AP. From each patient one buccal and rectal swab will be collected within 72 h after hospital admission. As primary endpoint we will analyze the association between microbial composition and the revised Atlanta classification. Secondary endpoints will be the association between microbiome signatures and length of hospital stay, numbers of interventions and mortality. For these analyses, alpha and beta diversity of microbiota will be determined and compared between mild, moderately severe and severe AP. If the analysis will reveal a set of microbes whose presence or abundancies are able to distinguish among the revised Atlanta classification (differential abundances), the microbiome could be employed as early clinical biomarker to guide clinical management of AP patients (e.g. early use of antibiotics).

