### Statistical methods

Prior statistical testing, normal distribution and homogeneity of variance will be examined using, QQ-plots and Levene’s test, respectively. If the data will be considered as normally distributed and the homogeneity is not violated, t-test for two groups and ANOVA with consecutive post-hoc tukey-type multiple comparisons for data with more than two groups will be performed. Non-normally distributed variables will be compared with Wilcoxon rank test (two groups) or non-parametric multiple comparisons (Kruskal–Wallis) for more than two groups. Statistical methods will compare groups for primary and secondary outcomes. For alpha diversity the following parameters will be calculated and presented in boxplots: Shannon-Index, Chao1-Estimator and observed richness (i.e. species). For beta diversity the following distances metrics will be performed: Bray–Curtis, unweighted and weighted UniFrac distances. The beta diversity will be visualized with principal coordinate analysis plot (PCoA). Significances will be calculated using PERMANOVA and pairwise adonis test. Further investigation of a significant distance in beta diversity will be conducted with high dimensional class comparisons using linear discriminant analysis of effect size (https://huttenhower.sph.harvard.edu/lefse/). Furthermore, a microbial network will be constructed after centered log-ratio transform of the out-table and visualized with Cytoscape.

Measures of diagnostic and predictive accuracy will be calculated, including area under the curve (AUC) and optimal cut-off point for classification (using simultaneous maximization of sensitivity and specificity).

Cox regression will be performed to interrelate length of hospital stay and the microbiome patterns, which will be calculated and will be most distinctive for the study population. 30-days mortality will also be analyzed using Cox-Regression with a calculated set of microbes as regressors. Number of interventions will be analyzed using negative binomial regression with the same microbes as regressors. Whenever feasible, 95-% confidence intervals will be provided for estimates.

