## Discussion

Early prediction of the course of AP remains challenging. We hypothesize that the orointestinal microbiome can be a potential biomarker for the course, severity and outcome of patients with AP. In line with our hypothesis, two small single-center studies from China detected alterations of fecal microbes which could distinguish between different grades of severities and between healthy volunteers and AP patients [20, 21]. With this prospective multicentric study we aim to investigate the microbiome in AP patients in a highly standardized and statistically powerful setting. To date, 8 centers are actively enrolling patients in P-MAPS. We intend to further expand the trial in Germany and involve large European centers. We not only focus on the intestinal microbiome but also analyze oral communities. There is emerging evidence that the oral flora plays a crucial role in pancreatic diseases, too [13]. In contrast to the existing data from China, we collect microbiome samples from rectal swabs but not from stool samples. Due to an oxygen gradient, there are different niches for microbes in the gut [27]. The microbial composition found in the lumen of stool fluctuates more frequently and harbors mostly anaerobic bacteria, whereas mucosa adherent microbes are often aerotolerant, more stable over time, and directly interact with the gut immune system [28, 29]. Thus, rectal swabs yield similar microbial communities as biopsies obtained by colonoscopy [30–33]. The longitudinal intraindividual stability of the microbial composition and the sufficient yield of biomass was confirmed before selecting rectal swabs as appropriate sampling method for the intestinal microbiome [31–33]. Therefore, it is widely accepted that rectal swabs are convenient and reliable alternatives to invasive biopsies.

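### The severity comparisons state no centre term or stratum, so centre differences in flora and case mix can appear as a severity effect

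*Protocol article*

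**What the plan says.** - **Aim.** Under Outcomes: "As primary endpoint we will analyze the association between microbial composition and the revised Atlanta classification".
- **Centres.** Study setting lists seven university hospitals and one district hospital, and adds: "The principal investigator intends to include more centers across Germany and Europe". The Discussion confirms the number: "To date, 8 centers are actively enrolling patients in P-MAPS".
- **Tests.** Statistical methods names, for normal data, "t-test for two groups and ANOVA with consecutive post-hoc tukey-type multiple comparisons for data with more than two groups will be performed", and otherwise: "Non-normally distributed variables will be compared with Wilcoxon rank test (two groups) or non-parametric multiple comparisons (Kruskal–Wallis) for more than two groups". For beta diversity: "Significances will be calculated using PERMANOVA and pairwise adonis test". LEfSe follows where beta diversity differs. Cox and negative binomial models with microbes as regressors serve length of stay, 30-day mortality and number of interventions. None of these carries a stated centre covariate, random effect or stratum.
- **Confounders.** Eligibility criteria says that antibiotic and probiotic intake, other drugs and reported diseases will be related to the microbiome patterns and so treated as potential confounders. Centre is not mentioned.
- **Handling.** Data collection methods stores swabs at −80 °C within three hours and processes all of them in one laboratory with one workflow. On transport it says: "External centers will ship samples on dry ice to Goettingen".

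**The concern.** Centre is the main grouping factor in this design, and it can be linked to both sides of the primary association. Hospitals of different type may admit different shares of moderately severe and severe cases. Patients from different regions, and later different countries, may carry different flora. Where both hold, severe cases are over-represented in some centres and bring those centres' flora with them. A test that treats all patients as exchangeable then attributes the centre difference to severity.

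A t-test, Wilcoxon or Kruskal–Wallis test has no place for a centre covariate. PERMANOVA can take a centre term and restricted permutations, but neither is stated. At stake is whether a significant difference in diversity or in individual taxa can be read as a marker of severity.

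**Working it through.** **The plan's own figure.** The stated power is 85% for an AUC of 0.8 against 0.7, with 100 per group and one-sided 2.5%. The Hanley–McNeil variance at A = 0.8 uses Q1 = A/(2−A) = 0.667 and Q2 = 2A²/(1+A) = 0.711:

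SE² = [0.16 + 99(0.667−0.64) + 99(0.711−0.64)]/10,000 = 0.000984, so SE = 0.0314.

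On the logit scale, with the null SE at 0.7 and the alternative SE at 0.8, power is 84.0%, which agrees with the plan. This figure has no centre component, so it does not settle the point.

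**Inputs for the centre question.** From the article: 400 patients, 25% non-mild (100/400), 8 centres. Assumed: 50 patients per centre, the spread of the non-mild share p across centres, and the fraction R² of microbiome variation explained by centre. The article gives none of the assumed values.

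**Formula.** With no severity effect, ignoring centre inflates the variance of the severity contrast by about

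λ = 1 + (m − 1) × R² × ρ, with m = 50 and ρ = V/[p̄(1 − p̄)],

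where V is the variance of p across centres and p̄ its mean. If either R² or ρ is zero, λ = 1 and there is no inflation.

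*Example.* Shares equally spaced from 10% to 40%: V = 0.00964, p̄(1−p̄) = 0.25 × 0.75 = 0.1875, ρ = 0.0514. At R² = 5%, λ = 1 + 49 × 0.05 × 0.0514 = 1.126. At R² = 10%, λ = 1.252. For a 20-dimensional composition the approximate rejection rate is P(χ²₂₀ > 31.41/λ), which gives 11% and 20%.

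**Simulation.** No severity effect, 8 centres of 50, 20 dimensions, 199 permutations, several sets of runs with 300 to 1,500 simulations per cell. Ranges are across sets.

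| Non-mild share by centre | ρ | R² | λ | Formula | Simulated, free permutation | Simulated, within centre |
|---|---|---|---|---|---|---|
| 15–35% | 0.023 | 5% | 1.056 | 7% | 5–8% | 3–5% |
| 15–35% | 0.023 | 10% | 1.112 | 10% | 9–10% | 5–6% |
| 10–40% | 0.051 | 5% | 1.126 | 11% | 10–14% | 4–6% |
| 10–40% | 0.051 | 10% | 1.252 | 20% | 16–21% | 4–6% |
| Seven at 27%, one at 10% | 0.017 | 5% | 1.041 | 7% | 5–7% | 4% |
| Seven at 27%, one at 10% | 0.017 | 10% | 1.083 | 9% | 8–9% | 4% |
| Two at 50%, six at 17% | 0.111 | 5% | 1.272 | 21% | 19–22% | 4–6% |
| Two at 50%, six at 17% | 0.111 | 10% | 1.544 | 44% | 28–43% | 4% |

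**A single variable, such as a diversity index.** The same λ inflates less in one dimension. The rate is 2[1 − Φ(1.96/√λ)], which is 6.5% and 8.0% for the 10–40% spread. A separate t-test simulation (3,000 runs per scenario) used a centre SD of 0.25 within-centre SDs, so R² = 0.0625/1.0625 = 5.9%. It rejected in 6.3% and 9.3% of runs for case-mix SDs of 0.5 and 1.0 on the logit scale. With a centre SD of 0.5 (R² = 0.25/1.25 = 20%) the rates were 9.9% and 20.4%. Within-centre comparison gave 4.7–5.5% in these four scenarios.

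**AUC.** In the t-test scenarios, up to a centre SD of 0.75, the 95th percentile of the AUC with no severity effect was at most 0.61, against 0.565 with no centre effects. That is well below 0.7.

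**The case against.** **An unseen analysis plan or full protocol may handle centre.** Covariates and permutation schemes are often left there, and the article does not say that its confounder list is complete. This stands in part: the permutation scheme is not given, and unrestricted permutation is an inference from silence. But the article does more than stay silent. It names tests that take no covariate for the group comparisons, and it states which variables are treated as confounders without including centre.

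**Handling is standardised.** One laboratory, one workflow, a three-hour freezing limit and dry-ice shipment reduce technical differences between centres. That stands. They do not touch differences in patients' flora or case mix.

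**The size is assumed.** This stands in full. Seven of the eight centres are university hospitals. Runs with only the district hospital differing gave little inflation (5–9%), though those shares are assumed too.

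**Stronger readings that a reader might infer:**
- *That the coordinating centre's swabs are not frozen.* The article stores swabs at −80 °C without exempting any centre; only the shipment differs.
- *That sequencing runs bias the comparison.* Run effects would do so only if runs were unbalanced by severity, and nothing in the article shows that.
- *That error rates of 20–40% are to be expected.* These need an extreme case mix or a large centre effect, for which the article gives no support.
- *That the predictive-accuracy target is compromised.* The AUC results above do not support this.

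**Conclusion.** The concern holds for centre. Followed as written, the group comparisons for the primary association exceed their nominal error whenever flora and severity mix both vary by centre, and the article gives no reason to rule out either. Under the assumed designs, with centre explaining 5–10% of variation, PERMANOVA error is about 5–10% for modest case-mix differences and about 10–20% for a 10–40% spread, against about 4–6% after adjustment. Single-variable tests are affected less at the same centre effect. Bias is possible, not demonstrated, and its actual size is unknown. The risk lies with PERMANOVA, the diversity comparisons and LEfSe rather than with the AUC. The change should be made because it is cheap and removes an obvious rival explanation of a positive finding. Intended European expansion may make it more relevant.

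**What to change.** In Statistical methods:

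1. Enter centre before severity in the PERMANOVA and pairwise adonis models, and restrict permutations to within centre.
2. Include centre as a fixed or random effect, or as a stratum, in the alpha-diversity, taxon-level and negative binomial analyses.
3. Stratify the Cox models by centre.
4. Add centre to the stated confounders, and give a rule for pooling very small centres, fixed before severity results are seen.

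No additional patients or samples are needed. The cost is a few degrees of freedom (seven for eight centres as a fixed effect) and slightly more analysis work. Centres with only mild or only non-mild cases contribute nothing to a within-centre comparison, which is why the pooling rule is needed.
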